### *Postnatal Depression*

Our primary measure is the Edinburgh Postnatal Depression Scale (EPDS; Cox, Holden & Sagovsky, 1987)(Appendix C) . The EPDS is a 10 item self-report scale designed to screen for postnatal depression in nonclinical populations. Participants give one of four possible responses to each of the ten statements. These possible responses indicate frequency, e.g. ranging from “Not at all” to “Yes, most of the time”, but the exact wording varies according to the statement. The scale typically takes around 5 minutes to complete (Cox et al., 1987).

The EPDS has been used widely in the National Health Service (NHS) as a screening tool for post-natal depression; and in previous studies in the field of maternal mental health and wellbeing (Leahy-Warren, McCarthy & Corcoran, 2012). A number of past studies found this scale to be a valid and reliable (Cox & Holden, 1994; Pope & Pope, 2000). In 2017, Cox published a 10 point supplement to their previous manual for this scale, designed to assist researchers in avoiding misuse of the EPDS (Cox, 2017). This study aims to follow both the manual for the scale (Cox, Holden & Henshaw, 2014), and this supplement (see Appendix D), in order to ensure standardised practice.

Because this measure is the primary screening tool for PND used in the NHS, if a participant scores above the clinical threshold implemented in the NHS, they will be sent a letter informing them of this, and encouraging them to access assessment and treatment for

postnatal depression via their GP or health visitor. This letter can be found in Appendix E.

At all three data collection time-points, information will be collected around whether participants are currently accessing pharmacotherapy or psychological care, using specific mental health-related items (please see Appendix B). This is in order to control for this variable during data analysis.

Recent studies have found that the sensitivity and specificity of the EPDS can vary between 59% to 100% and 44% to 97% (respectively) according to the geographic location of the study, the cutoff scores chosen by researchers, and the reference standards used for diagnosis (Novotney & Maurer, 2017).

Due to this variability in terms of sensitivity and specificity, some studies have recommended supplementing the EPDS with a second validated measure of depression that has shown less variation in sensitivity and specificity (Miller, Pallant, & Negri, 2006).

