### *Data Collection*

When their infant is 0 to 6 weeks old participants will complete baseline measures. For intervention participants completion of baseline measures will be prior to attending the sling surgery session. Currently these are due to include measures of PND (EPDS, DASS21), attachment (ECR-S), a measure of sling and buggy use and also of use of sling surgery services, a breastfeeding measure, and measures of wellbeing (WEMWBS/SWEMWBS), parenting (PSCS, CEQ), infant temperament (IBQ-R VSF) perceived social support (SPS) and general demographics (as mentioned in the *participants* section above).

As part of this feasibility study, it would be helpful to examine how long is needed before an effect of sling use upon maternal mental health, wellbeing and parenting may be seen. This information could support future RCTs in deciding the duration of a sling use intervention condition. It was agreed that an additional time-point, midway through the study, may help to narrow down the point at which an effect of sling use may be seen. Thus, 6 weeks

after completion of baseline measures, both intervention and control participants will be asked (via text or email - see below) to complete Time-2 (T2) measures online. These T2 measures are not the full battery of measures. Rather, participants in both groups will be asked about current sling use and use of sling surgery services (including whether they have swapped their sling). The EPDS will also be administered a second time at this time-point.

A further 6 weeks later (T3) participants in both conditions will be asked (via text or email - see below) to complete for a second time the full battery of measures that had been given at baseline (T1) (excluding demographic measures).

A text or email reminder (depending on each participant's stated preferred method of contact) will be sent each time that the participant is due to complete their next battery of measures. This message will contain a link to these measures (via Qualtrics).

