### *Ethical Implications*

Ethical approval will be sought from the University of Sheffield. As mentioned in the *Procedure* section above, during recruitment, participants will be given information explaining the aims and procedure of the study (please see Appendix Q). They will be asked to complete a consent form prior to participating in the study (Appendix R). It will be made clear that participants are free to withdraw their data at any time. Participants will also be debriefed at the end of the study (Appendix V).

As mentioned in the *Primary Measures* section above, during the study, it may be that participants score above the clinical threshold applied in NHS settings on the EPDS. Should this happen, participants will be sent a letter (please see Appendix E) recommending that they speak to their midwife or health visitor, and also their GP. The letter will be marked “Private and Confidential”.

It must be acknowledged that there is an incentive for participation in this study, in that participants in both conditions will receive sling hire and training for free, that they might have otherwise paid for. Furthermore, while control participants will receive the intervention (sling hire, training and support) following completion of the study, they will receive one month of free sling hire, support and training, the intervention participants will have received three months of free sling hire, support and training over the course of the study. While this discrepancy may appear unfair, it is commensurate with sling library advice and based on the different level of support needed in relation to infant age. Parents of very young infants usually require more support with sling use than parents of older infants.

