| 
1. I have been able to laugh and see the funny side of things
 

 As much as I always could

 Not quite so much now

 Definitely not so much now

 Not at all

 
2. I have looked forward with enjoyment to things
 

 As much as I ever did

 Rather less than I used to

 Definitely less than I used to

 Hardly at all

 
*3. I have blamed myself unnecessarily when things went wrong
 

 Yes, most of the time

 Yes, some of the time

 Not very often

 No, never

 
4. I have been anxious or worried for no good reason
 

 No, not at all

 Hardly ever

 Yes, sometimes

 Yes, very often

 
*5. I have felt scared or panicky for no very good reason
 

 Yes, quite a lot

 Yes, sometimes

 No, not much

 No, not at all

 | 
*6. Things have been getting on top of me
 

 Yes, most of the time I haven't been able to cope at all

 Yes, sometimes I haven't been coping as well as usual

 No, most of the time I have coped quite well

 No, I have been coping as well as ever

 
*7. I have been so unhappy that I have had difficulty sleeping
 

 Yes, most of the time

 Yes, sometimes

 Not very often

 No, not at all

 
*8. I have felt sad or miserable
 

 Yes, most of the time

 Yes, quite often

 Not very often

 No, not at all

 
*9. I have been so unhappy that I have been crying
 

 Yes, most of the time

 Yes, quite often

 Only occasionally

 No, never

 
*10. The thought of harming myself has occurred to me
 

 Yes, quite often

 Sometimes

 Hardly ever

 Never

 |

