**This letter will be sent to women who achieve a score of 13 or more when completing the EPDS at any time point.**

Dear [insert name],

You recently completed a set of questionnaires as part of your participation in the Sling Provision and Maternal Wellbeing study.

On one of the questionnaires, the Edinburgh Postnatal Depression Scale, the score you have suggests that you may be feeling low, tired or worried, following the birth of your child. It may be that you are suffering from postnatal depression, which is very common among families and underdiagnosed. There is help available if you are feeling this way. We recommend that you contact your GP, midwife or health visitor, to talk about these experiences, and seek further support.

Whatever you decide to do, whether you contact your GP, midwife or health visitor, or not, this will not impact on your participation in this study.

If you feel that at this point you would like to withdraw from the study, please feel free to do so, but please let us know by emailing the address below.

[[contact]](mailto:[contact])

Thank you and best wishes,

[name] and [name].

Sling Use and Maternal Wellbeing Project,

University of Sheffield.

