### S.6. Qualtrics Intro - All Time-points

**Introduction text that will be presented on Qualtrics at T1, T2, and T3. This is a template as the details will change slightly based on the time-point (this template applies to T1).**

Hello,

Thank you for agreeing to participate in this study.

You will now be asked to complete a series of questionnaires. These should take around **DURATION** to complete. These questionnaires will ask you about your mood, general wellbeing and experiences of parenting so far. You will also be asked demographic questions (e.g. age, ethnicity, postcode, education). Please read the instructions for each questionnaire carefully, as each questionnaire may ask you about a different time period (e.g. over the last week or over the last year etc.), or may give you different response options.

We do not anticipate that these questionnaires will cause you undue distress, but of course, talking about our mood, wellbeing or experiences of parenting so far can be an emotional process. We encourage you to take breaks if you need to. If you experience any difficult feelings while completing these questionnaires, and feel that you require support, please contact your GP.

Please remember that you can stop and withdraw your data at any point if you no longer wish to participate in this study.

Contact details:

Principal Investigator: [name], Trainee Clinical Psychologist,  
[[contact]](mailto:[contact])

Project Supervisor: [name], [[contact]](mailto:[contact]) Best wishes and thank you again,

[name].

University of Sheffield

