##### **How was this done?**

To do this, you were randomly allocated to one of two groups. If you were in the intervention group, you will have been given a baby sling at the beginning of the study, when your baby was 0-6 weeks old. You will have been asked to complete questionnaires three times; at the start of the study, after 6 weeks and after 12 weeks. These questionnaires included measures of postnatal depression, wellbeing, parental attachment style, and various aspects of the parenting experience (e.g. caregiving experience, sense of competency, social support).

If you were in the control group, you will have completed the same questionnaires, at the same times, but will have not been given a baby sling until after you had completed the final questionnaire at 12 weeks. This is so that we can look at whether there are any differences in the questionnaire scores between the two groups, and whether these differences change over time.

Talking about our mood, wellbeing or experiences of parenting so far can be an emotional process. If you experienced any difficult feelings while completing these questionnaires, and feel that you require support, please contact your GP or health visitor.

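### In the visible protocol the only score-triggered safety response is a letter at an EPDS total of 13 or more, so self-harm thoughts reported on item 10 with a lower total trigger no response of their own

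*Protocol*

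**What the plan says.** Appendix E sets the operative rule: "This letter will be sent to women who achieve a score of 13 or more when completing the EPDS at any time point". The body of the protocol uses the same basis. The Postnatal Depression section under Measures says that "if a participant scores above the clinical threshold implemented in the NHS, they will be sent a letter informing them of this", and Ethical Implications, on scores above the clinical threshold, says "Should this happen, participants will be sent a letter (please see Appendix E").

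The letter tells the woman that "the score you have suggests that you may be feeling low, tired or worried, following the birth of your child". It goes on to raise postnatal depression as a possibility, says that help exists, and recommends contact with the GP, midwife or health visitor. It does not mention self-harm.

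Item 10 in Appendix C reads "The thought of harming myself has occurred to me", with four answers from *Yes, quite often* to *Never*. The EPDS is in the baseline battery (T1) and in the repeat of that battery at T3. At T2, under Data Collection, "The EPDS will also be administered a second time at this time-point".

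Two visible texts give advice to every participant whatever her answers. The questionnaire introduction (Appendix S.6) says "If you experience any difficult feelings while completing these questionnaires, and feel that you require support, please contact your GP". The debrief sheet (Appendix V) carries similar wording, ending "feel that you require support, please contact your GP or health visitor".

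**The concern.** A screening total and a self-harm item answer different questions. The total summarises ten symptoms, while item 10 can call for a response on its own, even when the rest of the scale is unremarkable. A rule that looks only at the total can pass over a woman who reports frequent thoughts of self-harm while scoring low elsewhere. The protocol asks this question three times, so it should say what happens when the answer is not *Never*.

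What is at stake is participant safety. Nothing here bears on recruitment, retention or adherence estimates, or on the comparison between arms.

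**Working it through.** **Inputs**
- Trigger: EPDS total of 13 or more (Appendix E).
- Ten items with four answers each (Measures, Postnatal Depression; Appendix C).
- Scoring of 0 to 3 per item, total 0 to 30. This is an assumption, because the protocol prints no item scores.
- Planned sample of 50 to 60 women (Sample Size).
- Prices for envelope, postage and printing (Appendix Y).

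**Step 1: can item 10 be endorsed without a letter?** No letter is sent when item 10 plus the other nine items is 12 or less. The other nine can total 0 to 27.

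| Item 10 answer | Assumed points | Needed from the other nine to reach 13 | Other-nine totals that send no letter |
|---|---|---|---|
| *Hardly ever* | 1 | 13 − 1 = 12 | 0 to 11 |
| *Sometimes* | 2 | 13 − 2 = 11 | 0 to 10 |
| *Yes, quite often* | 3 | 13 − 3 = 10 | 0 to 9 |

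Every answer other than *Never*, including the most severe, is compatible with no letter.

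**Step 2: does another visible text respond to the answer?** The Appendix S.6 introduction comes before the questions, so it cannot react to a reply. The debrief is sent when T3 is completed, about 12 weeks after baseline, and that trigger does not reach a woman who stops earlier. The closing pages at T1 and T2 (Appendices S.7 and S.9 to S.11) cover the next questionnaires and, in the intervention arm, sling sessions or sling use. They contain no mental-health signposting. No visible section sets an item-level rule.

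**Step 3: how many women?** The documents give no rate for item 10, so the number cannot be estimated. As an illustration only, let q be an assumed share of women in this group. The chance of at least one among n women is 1 − (1 − q)^n:
- q = 1%: 40% (n = 50) to 45% (n = 60)
- q = 2%: 64% to 70%
- q = 5%: 92% to 95%

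These values of q have no source in the protocol. They show only that one such case could plausibly arise in a study of this size.

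**Step 4: cost of a posted letter at the protocol's prices.** £1.00/20 + £1.77 + £0.60/20 = £0.05 + £1.77 + £0.03 = £1.85. The 20 letters already budgeted come to £1.00 + £35.40 + £0.60 = £37.00.

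**The case against.** The strongest reply is that the protocol says it aims to follow the EPDS manual and its ten-point supplement. The supplement (Appendix D) asks for supervision by a trained health professional when the scale is used for assessment or screening, and for discussion of a mother's responses when she is assessed in the community. If the manual contains an item 10 instruction, the gap is narrower than it looks. This stands as a limit, because the manual is not shown. It does not remove the point: the supplement as reproduced has no item 10 rule, and a general aim does not override the explicit trigger in Appendix E.

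The information sheet and consent form (Appendices Q and R) and the closing part of the debrief sheet are also not shown, and detailed risk procedures may sit in the ethics application. A reader might infer that a woman below 13 certainly receives nothing but generic advice. The documents do not support that. They show only that no other response is visible.

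A reader might also infer that the letter reduces everything to low mood and tiredness. It does not, since it names possible postnatal depression and directs the woman to care. What it lacks is any reference to self-harm.

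Finally, a posted letter is a weak form of prompt response. The visible contact form (Appendix S.2) collects email and mobile number but no postal address, and Appendix V says contact details are destroyed once the debrief has gone out. That objection is sound, and it shapes the remedy.

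**Conclusion.** The point holds in a limited form. Followed exactly, the visible rule responds to a total of 13 but gives no targeted response to the most severe self-harm answer at a total of 12 or less. Lowering the cut-off alone would not cure this, because the letter does not address self-harm at any score.

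The conclusion rests on 0 to 3 item scoring and on the visible text; confidence is medium. The number of women affected is unknown. It is a gap in a safety procedure that Appendix E itself fixes, and not a statistical error. It is worth correcting because the remedy is cheap.

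**What to change.** Amend Appendix E so that any item 10 answer other than *Never*, at T1, T2 or T3, triggers a response whatever the total.

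- The existing team checks item 10 when it scores the EPDS. The item is already collected, and the scale must already be scored at each time point to apply the letter rule.
- The team promptly sends a version of the message that addresses thoughts of self-harm and urges early contact with the GP, midwife or health visitor. The amendment should say how soon.
- It goes by the email or mobile contact collected in Appendix S.2. At T3 the check and message must come before contact details are destroyed after the debrief.
- The same version is used for women at 13 or more who also endorse item 10.

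The cost is one added rule, one alternative text, and reading one more item at each scoring. The downside is a few extra messages, some prompted by mild answers such as *Hardly ever*. If any are posted, each costs about £1.85.

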## Appendix F Depression Anxiety and Stress Scales-21 (DASS-21; Lovibond & Lovibond, 1995).

| <h1 style="margin: 0;">DASS21</h1>                                                                                                                                                                                                                                                                                                                                                                                                                                                                                            |                                                                                                                                    | Name: | Date: |
|------------------------------------------------------------------------------------------------------------------------------------------------------------------------------------------------------------------------------------------------------------------------------------------------------------------------------------------------------------------------------------------------------------------------------------------------------------------------------------------------------------------------------------------|------------------------------------------------------------------------------------------------------------------------------------|--------------|--------------|
| 
Please read each statement and circle a number 0, 1, 2 or 3 which indicates how much the statement applied to you over the past week. There are no right or wrong answers. Do not spend too much time on any statement.
 
The rating scale is as follows:
 
0 Did not apply to me at all
           1 Applied to me to some degree, or some of the time
           2 Applied to me to a considerable degree, or a good part of time
           3 Applied to me very much, or most of the time
 |                                                                                                                                    |              |              |
| 1                                                                                                                                                                                                                                                                                                                                                                                                                                                                                                                                        | I found it hard to wind down                                                                                                       | 0            | 1 2 3        |
| 2                                                                                                                                                                                                                                                                                                                                                                                                                                                                                                                                        | I was aware of dryness of my mouth                                                                                                 | 0            | 1 2 3        |
| 3                                                                                                                                                                                                                                                                                                                                                                                                                                                                                                                                        | I couldn't seem to experience any positive feeling at all                                                                          | 0            | 1 2 3        |
| 4                                                                                                                                                                                                                                                                                                                                                                                                                                                                                                                                        | I experienced breathing difficulty (eg, excessively rapid breathing, breathlessness in the absence of physical exertion)           | 0            | 1 2 3        |
| 5                                                                                                                                                                                                                                                                                                                                                                                                                                                                                                                                        | I found it difficult to work up the initiative to do things                                                                        | 0            | 1 2 3        |
| 6                                                                                                                                                                                                                                                                                                                                                                                                                                                                                                                                        | I tended to over-react to situations                                                                                               | 0            | 1 2 3        |
| 7                                                                                                                                                                                                                                                                                                                                                                                                                                                                                                                                        | I experienced trembling (eg, in the hands)                                                                                         | 0            | 1 2 3        |
| 8                                                                                                                                                                                                                                                                                                                                                                                                                                                                                                                                        | I felt that I was using a lot of nervous energy                                                                                    | 0            | 1 2 3        |
| 9                                                                                                                                                                                                                                                                                                                                                                                                                                                                                                                                        | I was worried about situations in which I might panic and make a fool of myself                                                    | 0            | 1 2 3        |
| 10                                                                                                                                                                                                                                                                                                                                                                                                                                                                                                                                       | I felt that I had nothing to look forward to                                                                                       | 0            | 1 2 3        |
| 11                                                                                                                                                                                                                                                                                                                                                                                                                                                                                                                                       | I found myself getting agitated                                                                                                    | 0            | 1 2 3        |
| 12                                                                                                                                                                                                                                                                                                                                                                                                                                                                                                                                       | I found it difficult to relax                                                                                                      | 0            | 1 2 3        |
| 13                                                                                                                                                                                                                                                                                                                                                                                                                                                                                                                                       | I felt down-hearted and blue                                                                                                       | 0            | 1 2 3        |
| 14                                                                                                                                                                                                                                                                                                                                                                                                                                                                                                                                       | I was intolerant of anything that kept me from getting on with what I was doing                                                    | 0            | 1 2 3        |
| 15                                                                                                                                                                                                                                                                                                                                                                                                                                                                                                                                       | I felt I was close to panic                                                                                                        | 0            | 1 2 3        |
| 16                                                                                                                                                                                                                                                                                                                                                                                                                                                                                                                                       | I was unable to become enthusiastic about anything                                                                                 | 0            | 1 2 3        |
| 17                                                                                                                                                                                                                                                                                                                                                                                                                                                                                                                                       | I felt I wasn't worth much as a person                                                                                             | 0            | 1 2 3        |
| 18                                                                                                                                                                                                                                                                                                                                                                                                                                                                                                                                       | I felt that I was rather touchy                                                                                                    | 0            | 1 2 3        |
| 19                                                                                                                                                                                                                                                                                                                                                                                                                                                                                                                                       | I was aware of the action of my heart in the absence of physical exertion (eg, sense of heart rate increase, heart missing a beat) | 0            | 1 2 3        |
| 20                                                                                                                                                                                                                                                                                                                                                                                                                                                                                                                                       | I felt scared without any good reason                                                                                              | 0            | 1 2 3        |
| 21                                                                                                                                                                                                                                                                                                                                                                                                                                                                                                                                       | I felt that life was meaningless                                                                                                   | 0            | 1 2 3        |

